### Interventions

All patients will receive training 3 times weekly for 10 weeks. During each training session, patients in the control arm of the study will receive 40 min of self-training (sanding, placing, stretching, and repetitive reaching/grasping/releasing practice) and 20 min of usual care (conventional occupational therapy including stretching, joint range-of-motion exercises, correct-movement exercises, and ADL exercises). The RT group intervention will consist of the same 20 min of usual care, and 40 min of self-training with the ReoGo®-J upper-limb rehabilitation device (certification No. 226AHBZX00029000). The CT group intervention will include 40 min of self-training with robotic therapy and 20 min of CIMT training (shaping, task-practice, and transfer package).

### Outcomes

All outcomes will be measured at baseline, 5 and 10 weeks. The primary outcome examined will be changes in the FMA upper-limb score (9). This assessment examines motor and joint function, balance, and sensation in hemiplegic patients and results are represented as a numerical score with a maximum of 66 points.

Secondary outcomes include changes in: (1) the “amount of use” and “quality of movement” components of the MAL-14 scale (11), which assesses limb function in ADL; (2) the individual components of the FMA (9); (3) the ARAT score, another measure of upper-limb function (10); (4) the motricity index (26), an assessment of muscle strength in stroke patients; (5) the MAS score (20), which assesses muscle tone (i.e., spasticity); (6) the active range of motion of the shoulder, elbow, forearm, wrist, and fingers (27); and (7) the Stroke Impact Scale (28), a quality of life assessment scale for stroke patients.

Safety outcomes will include the occurrence of any adverse events. Adverse events will be assessed as either related or unrelated to the study treatment, and their severity graded using the CTCAE Ver 4.03 (29) as a reference. All adverse events will be recorded on the medical chart and case report form. In the case of serious adverse events, including those that are life-threatening or result in hospitalization, a “serious adverse event and malfunction report” will be prepared by the investigator and submitted to the hospital director promptly.

### Data monitoring and management

The research director is responsible for monitoring the study, including ensuring that the data reported by the investigators are accurate, complete, and verifiable in comparison with the source documents and other records. An operating procedure for monitoring will be prepared by the principal investigator in advance, and the principal investigator shall appoint monitors to conduct this monitoring as appropriate. At each hospital, the investigator and the hospital director shall cooperate with all investigations by a monitor, the institutional review board, or a regulatory authority. The investigator and director must present all study-related records, such as source documents, when requested by the investigating body.

Because this study uses a medical device that has received marketing approval, together with the nature of the interventions and the sample size, specific quality assurance audits do not need to be planned. Rather, routine data monitoring as described above will ensure data quality.

The electronic case report form will be provided by the data center of the Tsukuba Clinical Research and Development Organization (T-CReDO). The data center will also perform quality control of the collected data, specifically by conducting logical checks. In cases where inconsistencies, missing values, or other issues are detected in the entered data, the investigator will be queried, and they will revise the electronic case report form if necessary. After completion of data quality control, a case review will be convened. The data center will create a dataset for analysis and transfer quality control records and datasets to the study statistician.

The investigator and director of each hospital are responsible for retaining all records, and the data center will retain the anonymized, transcribed case report form data. These data will be retained for 5 years after completion or termination of the study or 3 years after the last publication of results from the study, whichever is later, unless an individual study site has established a longer retention period.

### Confidentiality

Data such as subject information and data collected from observations and examinations will be stored as an anonymized, linkable dataset using identification codes within the data center. Each participating study site shall manage the coding keys linking identification codes to respective subjects within its facility. All individuals involved in the study will take care to protect subjects' identifying information when handling documents, anonymizing case report forms, and incorporating data into publications.

### Data access and dissemination

Subjects in this study may obtain or access the protocol and study-related documents by making a request to the treating physician, provided that doing so would not hinder the protection of personal information of other subjects or the assurance of originality of this study. After study completion, the principal investigator shall organize and publish the results promptly in an academic journal or academic conference, among other media. The ownership of any papers or presentations prepared using the data collected in this study shall be decided through consultations with the principal investigator. Any copyright will be shared by the lead author and coauthors.

### Sample size

The principal objective of the study is to verify the superiority of the RT group over the control group in the improvement of FMA upper-limb score. Using the minimal clinically important difference (MCID) as a reference, the mean difference between the patients in the RT and control groups with respect to the FMA upper-limb score is expected to be 4.25 points (30). Given that the subjects in this study will be chronic patients, the deviation is expected to be smaller than that in the pilot study conducted in recovering patients (standard deviation, 8.8) (6), and thus a standard deviation of 6 is expected. Based on a two-sided significance level of 0.05 and a power of 0.9 on Student's *t*-test, a sample size of 39 per group is needed. Considering some loss to follow-up, the sample size was increased from 39 to 40 per group. Additionally, in our similar previous study (6), we recruited 56 case in 6 facilities (about nine case per a facility). Therefore, considering difficulty to recruited case in chronic stage, we judged this study will be feasible to request more than 20 facilities to participate this study.

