For the each of the various measures we will use to assess rehabilitation, the MCID has been established. Of the measures that quantify general hemiplegic arm function, the MCID for FMA is 4.25–7.25 points (30), and that of the ARAT is 10% of the total score (10), or 5.7 points (35). The MCID of MAL, which measures the use of the affected arm in actual life, is 0.5 points for the amount of use scale (36) and 1.0–1.1 points for the quality of movement scale (37). Because clinical resources are limited, there are few interventions/approaches to achieve MCID in the measures of arm function and arm use. However, our pilot studies have shown that combined robot and CIMT therapy could improve arm function and use of the affected arm, and those increases were greater than MCID (38, 39). Those results suggest we will see a promising effect of CT in this ReoGo-J study, and that the combined therapy will overcome the weakness of robotic therapy and significantly increase the use of affected arm in real-life settings.

Currently in Japan, many elderly stroke patients receive one-on-one rehabilitation by physical or occupational therapist 20 min per day at an adult day-care center run by the long-term care insurance system. The protocol of the control group in this study is expected to represent the conventional rehabilitation usually done at such adult day-care center. Therefore, if this study proves RT or CT group exceeded control group, we could suggest a better protocol for rehabilitation for upper extremity hemiparesis for chronic stroke patients at adult day-care center. Furthermore, our suggestion may increase the recovery of upper extremity function and use of affected arm at the same resources and cost as conventional protocol.

However, there are some limitations in this study. For example, there are many factors affecting the prognosis of upper extremity hemiplegia caused by stroke: age, sex, baseline upper extremity motor function, time after stroke, degree of sensory deficit, patients' degree of motivation, family support, various approaches within robotic therapy and CIMT (i.e., types of movement, repetitions, clinical site). In this study, the allocation factor will be set based on previous studies to control for differences in the following characteristics between groups: (1) baseline FMA score (40), (2) time after stroke (41–43), (3) age (43, 44), and (4) clinical site. However, the other factors cannot be controlled by this method.

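### The stated power of 0.9 is not delivered by 40 per group even at the planned SD of 6 (it is about 88%), and it falls steeply if the SD lies above 6, a value supported only by a qualitative argument

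*Protocol article*

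**What the plan says.** The Sample size section of the protocol article names the comparison that the trial is sized for: "The principal objective of the study is to verify the superiority of the RT group over the control group", on improvement in the FMA upper-limb score. It takes a mean difference of 4.25 points, with the minimal clinically important difference (MCID) as reference, and presents it as the expected difference. The Discussion gives the cited MCID as a range from 4.25 to 7.25, so 4.25 is its lower end.

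For variability, the section quotes one observed figure and then departs from it. "Given that the subjects in this study will be chronic patients", it argues, "the deviation is expected to be smaller than that in the pilot study conducted in recovering patients (standard deviation, 8.8", "and thus a standard deviation of 6 is expected". It does not say whether 8.8 is the SD of the change or of the score, and it gives no SD from a chronic population.

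From these inputs, with a two-sided level of 0.05, a power of 0.9 and Student's t-test, it derives 39 per group. It raises this to 40 for loss to follow-up.

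**The concern.** There are two problems with the single power figure. First, 0.9 does not follow from the plan's own inputs at the size chosen. Second, it rests on an SD for which the article gives a direction and no number. Going from 8.8 to 6 removes more than half of the variance, since 1 − (6/8.8)² = 0.54. An argument that chronic patients vary less would fit 7 or 8 as well as it fits 6.

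The stated power tells readers how likely the trial was to detect 4.25 points on its principal objective. If the SD turns out at 7 or 8, that chance is well short of the figure printed, and nothing in the article would tell a reader so. The allowance for loss is one patient per group, so there is no slack in the numbers to absorb a larger SD.

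**Working it through.** **Inputs** (Sample size section unless noted): difference 4.25; planned SD 6; pilot SD 8.8; two-sided α = 0.05; target power 0.9; Student's t-test; 39 per group, raised to 40. The total of 120 in three groups (Study design) is taken as 40 per group.

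**Step 1: the plan's own figure.** By the normal approximation, n per group = 2 × [SD × (z₀.₉₇₅ + z₀.₉₀) / difference]² = 2 × [6 × (1.960 + 1.282) / 4.25]² = 41.9, so 42. The exact t-test (noncentral t) needs 43: power is 89.4% with 42 per group and 90.1% with 43. A one-sided 0.05 test by the normal approximation would need 35. None of these gives 39.

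**Step 2: power at the planned size.** The noncentrality is 4.25 / (SD × √(2/40)), with 78 degrees of freedom. At SD 6 it is 4.25 / (6 × 0.2236) = 3.17, which gives power 87.9%. With 39 analysed per group, the power is 87.0%. For 40 per group to give 90%, the SD would have to be about 5.8.

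**Step 3: power over the range from the planned to the pilot SD** (difference 4.25, exact t).

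| SD | Noncentrality, 40 per group | Power, 40 per group | Power, 39 per group | n per group for 90% |
|---|---|---|---|---|
| 6 | 3.17 | 88% | 87% | 43 |
| 7 | 2.72 | 76% | 75% | 58 |
| 8 | 2.38 | 65% | 64% | 76 |
| 8.8 | 2.16 | 57% | 56% | 92 |

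**Step 4: where power passes 80%.** Solving the same expression for the SD at 40 per group gives about 6.7. An SD only 0.7 above the planned value is enough to bring power to 80%.

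All figures use the unadjusted 0.05 level, as the plan's own calculation does.

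**The case against.** The strongest reply is that 8.8 is the wrong yardstick. It comes from recovering patients. This trial takes patients at least 6 months after stroke with an FMA score below 44, and excludes those whose arm function is judged to be improving. All of this plausibly narrows the spread of changes. If 8.8 is an SD of scores, it does not describe the analysis of change at all. The planned model also adjusts for baseline FMA; on the assumption that 8.8 is a score SD, a baseline correlation of √0.54, about 0.73, would by itself bring 8.8 down to 6. The basis for 6 may also stand in the full protocol, which is not shown. This part of the reply stands: a smaller SD is plausible, and 57% is a worst case. It does not rescue the stated 0.9, which is missed at SD 6 itself, and it does not turn a direction into a value.

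Three stronger readings are tempting but not supported.

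- A reader might argue that chronic patients should also show a smaller treatment difference, so that 4.25 had to shrink with the SD. A difference anchored to an MCID is a target, and a target need not shrink. The valid remainder is that the article calls it expected.
- A reader might take the Discussion's remark that "there are few interventions/approaches to achieve MCID in the measures of arm function and arm use" as an admission that 4.25 is out of reach. That sentence opens by attributing the shortage to limited clinical resources and says nothing about the difference between RT and control.
- A reader might infer that at SD 8.8 a null result could not exclude 4.25. The 95% half-width there is 1.991 × 8.8 × √(2/40) = 3.92, so an estimate of zero would exclude it.

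**Conclusion.** The point holds as a correction to a stated figure. On the plan's own inputs, 40 per group gives about 88% power, not 90%. Over the range from the planned SD to the only observed one, power runs from 88% to 57%, and it falls below 80% above an SD of about 6.7. These results assume a true difference of 4.25, 40 analysed per group, equal variances and an unadjusted two-sided 0.05 t-test. Loss to follow-up would lower them; baseline adjustment could raise them by an amount the article does not let one calculate.

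It would go too far to conclude that the SD of 6 is wrong or that the trial has 57% power. The documents establish neither. They show only that the value 6 is unsupported in the article and that the stated power is sensitive to it.

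**What to change.** Make three changes in the Sample size section:

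1. Replace the single power of 0.9, and the 39 per group said to deliver it, with the power that 40 per group gives: about 88% at SD 6, before any loss to follow-up.
2. Add the power at 40 per group over SD 6 to 8.8: 88% at 6, 76% at 7, 65% at 8 and 57% at 8.8. Identify 8.8 as the pilot value from recovering patients.
3. Describe 4.25 as the target difference, set at the lower end of the cited MCID range, and not as the expected difference.

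This changes wording only. Enrolment, allocation and the analysis model stay as they are, and no extra patients are needed. The downside is a less favourable stated power.

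### The stated inputs require 43 patients per group, not 39, so 40 per group falls short of the stated 90% power even with no dropout

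*Protocol article*

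**What the plan says.** The Sample size section of the protocol article prints every input of a two-group comparison of means.

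- Aim: to "verify the superiority of the RT group over the control group in the improvement of FMA upper-limb score".
- Difference: the mean difference "with respect to the FMA upper-limb score is expected to be 4.25 points", taken from the minimal clinically important difference.
- Standard deviation: the text refers to "the pilot study conducted in recovering patients (standard deviation, 8.8"), argues that chronic patients should vary less, "and thus a standard deviation of 6 is expected".
- Error rates: "Based on a two-sided significance level of 0.05 and a power of 0.9", on Student's t-test.
- Result: "a sample size of 39 per group is needed".
- Allowance: for some loss to follow-up, with no rate given, "the sample size was increased from 39 to 40 per group".

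Study design gives the total of 120 patients in three groups, which matches 40 per group.

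**The concern.** With the difference, standard deviation, significance level, power and test all stated, the sample size is fixed, and 39 is not the number that follows. The gap is three to four patients per group, more than rounding or choice of software would explain.

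The single patient added for loss does not close the gap. Forty is already below what the inputs require, so the step from 39 to 40 leaves no real margin for loss. Taken at face value it allows for 1/40 = 2.5% loss. The trial runs to 30 sessions (three a week for 10 weeks, Interventions), and its withdrawal grounds are broad (Withdrawal from study).

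At stake is how a null result for RT against control would be read. Readers would assume a 10% chance of missing a true 4.25-point difference, whereas on the stated inputs the chance is 12% or more.

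**Working it through.** **Inputs**, all from the Sample size section: difference d = 4.25; SD s = 6; two-sided α = 0.05; power 0.90; two-sample Student's t-test with equal groups of n.

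**Step 1. Normal approximation.**

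n = 2 (z₀.₉₇₅ + z₀.₉₀)² s² / d² = 2 × (1.960 + 1.282)² × 36 / 18.0625 = 41.9, so 42 per group.

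**Step 2. Exact t-test, the test the text names.** Power comes from the noncentral t distribution with 2n − 2 degrees of freedom and noncentrality (d/s)·√(n/2) = 0.7083·√(n/2).

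| n per group | Noncentrality | Critical t | Power |
|---|---|---|---|
| 39 (stated need) | 3.128 | 1.992 | 0.870 |
| 40 (planned) | 3.168 | 1.991 | 0.879 |
| 42 | 3.246 | 1.989 | 0.894 |
| 43 | 3.284 | 1.989 | 0.901 |

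The smallest n that reaches 0.90 is 43.

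**Step 3. Can 39 be reproduced another way?**

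| Variant | n per group, exact t | Gives 39? |
|---|---|---|
| One-sided 0.05, power 0.90 | 35 | No |
| Two-sided 0.025 (Bonferroni for two comparisons), power 0.90 | 51 | No |
| Two-sided 0.025, power 0.80 | 40 (38 by normal approximation) | No |
| Two-sided 0.05, power 0.85 | 37 | No |
| Two-sided 0.05, power 0.87 | 39 | Only at a lower power than stated |
| Difference 4.5 instead of 4.25 | 39 | Only with a different effect |
| SD 5.7 instead of 6 | 39 | Only with a different SD |

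Pooling the error degrees of freedom over three groups raises power at 39 only to 0.873. In every case tried, reaching 39 means changing a stated input.

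**Step 4. What 40 per group delivers.**

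- All 40 evaluable: power 0.879, so a 12% chance of missing the effect.
- 10% loss (assumed), 40 × 0.90 = 36 evaluable: power 0.842, a 16% chance of missing it.
- 15% loss (assumed), 40 × 0.85 = 34 evaluable: power 0.821, an 18% chance of missing it.
- Difference detectable with 90% power at n = 40 and SD 6: 4.40 points.

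**Step 5. Sensitivity to the SD.** With the pilot SD of 8.8, which the text sets aside with a reason, power at 40 per group would be 0.57. This shows how much rests on the choice of 6. It plays no part in the arithmetic error.

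**The case against.** Nobody disputes the arithmetic; the case on the other side is about how much it matters.

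**The shortfall is small.** At 40 per group, power is 87.9% by the exact test and 88.6% by the normal approximation, and the detectable difference rises by 0.15 points on a 66-point scale. This stands: the loss of power at full follow-up is modest. It does not make the printed figure right.

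**The planned analysis is not a t-test.** Statistical analyses specifies a mixed model adjusted for baseline FMA, among other terms, which could recover power. If the covariates had a multiple correlation r with the change score, the residual SD would be 6·√(1 − r²). Power at 40 would then be about 89.1% for r = 0.2, 90.7% for r = 0.3 and 92.7% for r = 0.4. This stands in part. It means the check shows that the stated calculation fails, not that the planned model must fall below 90%. But the article gives no such correlation and bases its number on the unadjusted t-test, so the adjustment cannot justify 39. The Dunnett adjustment in the same section pulls the other way. If it applies to RT against control (critical value about 2.24), power at 40 per group is about 82%. That is a separate point, and this finding does not depend on it.

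**The loss rates are assumptions.** Withdrawn patients are to have end-of-study examinations where possible, and the repeated-measures model also uses week 5 data, so withdrawal from training need not remove a patient. This stands: the 10% and 15% cases are illustrations. The shortfall at 40 per group exists with no loss at all.

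**Conclusion.** The concern holds. On the article's own inputs the requirement is 43 per group by the exact t-test (42 by the normal approximation), so the stated 39 is 4 too few and the planned 40 is 3 too few. Power on the stated test is 87.0% at 39 and 87.9% at 40, against the 90% claimed.

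This conclusion rests only on the printed difference, SD, significance level, power and test. The figures under loss also rest on assumed rates and on complete removal of the lost patients. The error in the stated sample size is clear, and its effect on power is modest unless losses are substantial. It needs correcting because it is a wrong statement about the power of the principal comparison, and a full protocol or analysis plan could not put it right by adding detail.

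**What to change.** Correct the Sample size section in one of two ways.

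1. State that 43 evaluable patients per group are needed for 90% power. If 90% is also to be delivered, three groups need 3 × 43 = 129 evaluable patients plus an allowance for loss. At an assumed 10% loss that is 43/0.90 = 47.8, so 48 enrolled per group.
2. Keep 120 patients and restate the power as about 88% with 40 evaluable per group and about 84% at an assumed 10% loss. Give 4.40 points as the difference detectable with 90% power at 40 per group.

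In either case, state the loss rate assumed. If an adjustment for baseline or a different input lay behind 39, state it with its value so that the number can be reproduced. The same revision should make the significance level used for sizing agree with the multiplicity adjustment in Statistical analyses.

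The second option costs only wording: the power claim becomes slightly less favourable and no extra patients are needed.

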### Study design

This study will be conducted as a multi-center, prospective, randomized, parallel group study. We aimed to enroll 120 chronic stroke patients from approval by the institutional review board until March 31, 2017. The chronic stroke patients enrolled will be randomized to three groups: a control group to receive conventional occupational therapy (usual care) and self-training that follows the concept of usual care; a group to receive usual care and self-training with robotic therapy; and a group to receive combination training that includes task-oriented training aimed at improving function in ADL and robotic therapy.

The principal investigator will register the study on the clinical trial registration system of the University Hospital Medical Information Network (UMIN000022509) after approval of this study by the clinical research institutional review board of the Hyogo College of Medicine (#2248) and before enrolling subjects.

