### Withdrawal from study

Patients will be withdrawn from the study if they undergo certain prohibited therapies after enrolling in the study. These include functional electrical stimulation, transcranial magnetic stimulation, and transcranial direct current stimulation. Training with any other upper-limb rehabilitation robot is also prohibited after informed consent. Patients must not receive botulinum toxin injections during the treatment period.

The investigator can decide to withdraw an enrolled and allocated patient from this study if they have difficulty beginning or continuing study participation, such as failure to attend study visits, withdrawal of informed consent, adverse events or complications, recovery of arm function so that no further rehabilitation is needed, or any other event judged by the investigator to warrant withdrawal. The investigators, after withdrawing a subject, shall perform the planned end-of-study examinations to the extent possible and record the observations, last date of training, and reasons for withdrawal on the case report form.

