### Statistical analyses

Two analysis populations will be established: the safety analysis set and the efficacy analysis set. The safety analysis set will include all patients who were allocated, and the numbers and percentages of safety endpoints will be compared between groups by Fisher's exact test.

The subject characteristics collected upon enrollment will be analyzed by intergroup comparisons of continuous variables by analysis of variance and of categorical variables by Fisher's exact test.

The efficacy analysis set will include all patients for whom primary endpoint data are available based on intention-to-treat principle. Using the mixed effects model for repeated measures, we will perform intergroup comparisons of changes in the FMA upper-limb score at 5 and 10 Weeks of the treatment phase. This model will include the group, time point, group-by-time interaction term, baseline FMA upper-limb score, sex, and botulinum toxin injection. For multiplicity adjustment, Dunnett's test will be employed with the RT group used as a reference. The same analysis will be conducted for the secondary outcomes. The level of significance is set at 0.05.

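### The stated 90% power is not reached at 40 per arm even with no loss, and the one-patient allowance for loss (2.5%) has no stated basis

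*Protocol article*

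**What the plan says.** The Sample size section of the protocol article sizes the trial for RT against control. The mean difference in "the FMA upper-limb score is expected to be 4.25 points", and "a standard deviation of 6 is expected". "Based on a two-sided significance level of 0.05 and a power of 0.9" on Student's t-test, it concludes that "a sample size of 39 per group is needed". It then adds: "Considering some loss to follow-up, the sample size was increased from 39 to 40 per group". No loss rate and no source for one are given. Study design sets the total at 120 in three groups.

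Three other sections bear on how many patients will be analysable:

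- **Interventions:** three sessions a week for 10 weeks, so 30 sessions.
- **Withdrawal from study:** certain prohibited therapies lead to withdrawal. The investigator may also withdraw a patient for reasons "such as failure to attend study visits, withdrawal of informed consent, adverse events or complications, recovery of arm function", or for any other event judged sufficient. End-of-study examinations are still to be done after withdrawal, as far as possible.
- **Statistical analyses:** "The efficacy analysis set will include all patients for whom primary endpoint data are available", on the intention-to-treat principle, with a mixed model for repeated measures on the week-5 and week-10 changes.

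**The concern.** The plan presents 39 as the number needed for 90% power and 40 as that number protected against loss. An allowance of one patient means that a second patient without endpoint data in an arm takes that arm below 39. For a 10-week, 30-session outpatient programme with several routes to withdrawal, this is a thin margin, and nothing in the article supports it.

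A reader will take 90% as the power of the principal comparison, loss included. If the trial then finds no difference between RT and control, that figure decides how much weight the result bears. It should therefore be the power that the design delivers.

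**Working it through.** **Inputs.** From Sample size: difference 4.25, SD 6, two-sided alpha 0.05, power 0.90, Student's t-test, 39 needed, 40 randomised per arm. The loss rates below are assumptions, because the documents give none. Here *loss* means a patient with no usable endpoint data, which is narrower than withdrawal.

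**1. The plan's own figure.** The normal approximation is n = 2 × [SD × (z₀.₉₇₅ + z₀.₉₀) / difference]² = 2 × [6 × (1.960 + 1.282) / 4.25]² = 41.88, so 42 per group. The exact two-sample t-test (noncentral t, 2n − 2 degrees of freedom, noncentrality 4.25 / (6 × √(2/n))) gives 89.4% at 42 and 90.1% at 43, so 43 per group. The stated 39 is not reproduced.

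**2. Power at the numbers in question** (same exact t-test, unadjusted):

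| Analysable per arm | Corresponds to | Power | Change from 39 |
|---|---|---|---|
| 40 | no loss | 87.9% | +0.8 |
| 39 | 2.5% loss (40 × 0.975) | 87.0% | 0 |
| 38 | 5% loss (40 × 0.95) | 86.2% | −0.9 |
| 36 | 10% loss (40 × 0.90) | 84.2% | −2.8 |
| 34 | 15% loss (40 × 0.85) | 82.1% | −5.0 |

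Changes are taken from unrounded values.

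**3. Splitting the shortfall from 90%.** At 39 the gap is 90.0 − 87.0 = 3.0 points, and it comes entirely from the base of 39. Loss beyond the allowance adds 0.9, 2.8 or 5.0 points at 5%, 10% or 15%. At 5% loss most of the gap is therefore the wrong base; at 10% the two parts are about equal; at 15% loss is the larger part.

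**4. Chance that the allowance is exceeded.** The allowance is 1/40 = 2.5%. With loss rate d, independent between patients, an arm keeps at least 39 of 40 with probability P = (1 − d)⁴⁰ + 40 × d × (1 − d)³⁹. The chance that RT or control falls below 39 is 1 − P².

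| Assumed loss d | P, one arm keeps ≥39 | P², both keep ≥39 | RT or control below 39 |
|---|---|---|---|
| 1% | 0.939 | 0.882 | 12% |
| 2.5% | 0.736 | 0.541 | 46% |
| 5% | 0.399 | 0.159 | 84% |
| 8% | 0.159 | 0.025 | 97% |
| 10% | 0.080 | 0.006 | 99.4% |
| 15% | 0.012 | <0.001 | over 99.9% |

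Even if true loss equals the 2.5% that the allowance implies, a shortfall in one of the two primary arms is close to an even chance.

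**The case against.** **No loss rate is given.** A reader might infer from the list of withdrawal reasons that 39 per arm will almost surely be missed. The documents do not support that. A list of reasons is not a rate, and the inference needs a true loss of roughly 8% or more; at 1% the chance of a shortfall is only 12%. This objection stands, and the probabilities above are conditional on assumed rates.

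**Withdrawal is not the same as lost data.** Examinations are to be done after withdrawal where possible, the efficacy set keeps everyone with primary endpoint data, and the mixed model uses week-5 values. A patient withdrawn for recovery or a prohibited therapy may still be measured. This also stands and lowers the effective loss. It does not remove it: a patient who stops attending or withdraws consent may supply nothing further, and a week-5 value only partly replaces one at week 10.

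**The power cost of loss is modest and partly belongs to another error.** A reader might set 82% to 86% against 90% and blame loss for the whole difference. That is wrong, since about 3 points are already missing at 39.

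**The t-test is not the planned analysis.** Baseline adjustment and the week-5 data tend to raise power, and the Dunnett adjustment lowers it; the documents do not allow the net effect to be calculated. But the t-test is the basis on which the plan states its 90%, so it is the fair basis for checking that figure.

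**A condensed article may leave the rate's justification to the full protocol.** That is fair for the justification alone. It does not cover a stated power that the article's own inputs fail to give.

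**Conclusion.** The point holds in a limited form. On the plan's own inputs, 40 randomised per arm do not give 90% power at any loss rate: the figure is 87.9% at best, and 86.2%, 84.2% or 82.1% if 5%, 10% or 15% have no usable endpoint data. The allowance of one patient per arm has no stated basis and is fragile, with a 46% chance of a shortfall in RT or control at 2.5% loss and 84% at 5%. Of the gap to 90%, about 3 points come from 39 being too low, and loss adds about 1 to 5 points relative to 39.

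The conclusion rests on an unadjusted t-test, the plan's difference and SD, independent losses, and loss rates that are assumed. The point is worth correcting because the stated power is relied on and the correction is cheap. It does not show that the trial is unsound.

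**What to change.** In the Sample size section of the protocol:

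1. Replace the unspecified loss with a rate that is labelled as an assumption.
2. Give the analysable number expected from 40 randomised per arm at that rate, for example 38, 36 or 34 at 5%, 10% or 15%.
3. Replace the 90% with the power at that number: about 88% at best, and 82% to 86% across 5% to 15% loss.
4. Correct the base of 39 in the same edit, since the stated inputs need 43 per group by the t-test (42 by the normal approximation). Naming a loss rate while leaving 39 and 90% in place would not repair the statement.

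The target of 120 can stay, so no extra enrolment is needed. The only cost is a less favourable stated power.
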